### Data collection and management

2.11

The evaluation of the curative effect and data collection will be carried out by members of the research group except the operator. The symptoms of milk deficiency and TCM symptoms will be evaluated when the patients are enrolled in the group and after each treatment. It will be recorded 6 times. In addition, subject's serum prolactin levels should be measured at the time of entering the group and after the end of whole treatment. First, the evaluator will use the paper version of the evaluation form to record data, and then enter the data into excel form for management. The original case report form and all other forms (including consent forms) will be archived securely in the obstetrics department of Chengdu University of TCM.

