**Methods::**

This is a 2 parallel-group, assessor-blinded, randomized controlled trial.128 patients with lactation insufficient after cesarean section will be recruited and randomly divided into control group and the pestle needle group in a 1:1 ratio. The control group will receive routine nursing care of milk deficiency. In the pestle needle group, pestle needles will be used to operate on the acupoints such as bilateral Shao ze (S11), bilateral Ru gen (ST18), Dan zhong (DU14), 8 array acupoints of Shen dao (DU11) and so on. It will be operated once a day for 5 days. The primary outcomes are milk yield, degree of breastfilling, degree of milk siltation and other milk deficiency symptom, and serum prolactin. Secondary outcomes include syndrome of traditional Chinese medicine, such as facial expression, fatigue, loss of appetite, and so on.

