### Randomization and blinding

2.5

The randomization sequence will be generated by computer using excel software (Excel 2010 developed by Microsoft; Washington, DC), and using block randomization with a block size of 4 via a central randomization system. Put the random distribution card into opaque envelopes and number the envelopes. The number of the envelopes is the same as that of the random distribution card. When qualified subjects enter the study, open the envelopes in order and carry out treatment according to the grouping. The randomized scheme will be designed by a nursing graduate student in the research group, who will not participate in the clinical implementation phase of the study. Data collectors and statistical analysts will not know the grouping of patients. It is a pity that patients and operators could not be blinded in this study.

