### Interventions

2.6

According to the literature review and pestle acupuncture therapy,^[20,21]^ the following necessary acupoints are selected:bilateral Shao ze (S11), bilateral Ru gen (ST18), Dan zhong (RN 17), 8 array acupoints of Shen dao (DU11) which is formed with Shen dao (DU11) as the center and 3 cun as the radius., Heche Road of Da zhui (DU14) to Zhi yang (DU9). And then, add other acupoints according to different syndrome types of lactation insufficiency. Bilateral Zu san li (ST36) andbilateral Xue hai (SP10) will be used for type of deficiency of qi and blood. Bilateral Tai chong (LR3) and bilateral Qi men (LA14) will be used for type of liver qi stagnation (Table 1). Treatment will be performed with Taiji pestle needle tool which was designed by Li's pestle needle inheritance studio of Chengdu University of TCM. The needle is a patented product and its patent number is 89213016.4. The operator use pestle tool 1 or pestle tool 2 to knock on and stimulate S11, ST18, RN 17, ST 36, SP 10, LR 3, and LA 14 down to the point that the patient can bear, and then relax gently. Next, use pestle tool 3 to stick on the skin and repeatedly draw an S-shaped or 8-shaped figure in 8 array acupoints of Shen dao. Last, The operator use pestle tool 4 massage along the Heche Road of DU14 to DU9. Each treatment lasts 30 minutes, and the strength of the operation should be a slight flush on the skin. Operators need to receive professional training in the operation of pestle needles in advance.

**Table 1 T1:** Locations for acupuncture.

Acupoint	Location
ST18 (Ru gen)	Below the nipple, at the root of the breast, the fifth intercostal space, 4 cun from the anterior median line
ST 36 (Zu san li)	Three cun directly below ST35, and 1 finger-breadth lateral to the anterior border of the tibia
S 11 (Shao ze)	On the ulnar side of the distal segment of the little finger, and 0.1 cun from the nail angle
LR 3 (Tai chong)	On the dorsal side of the foot and in the depression in front of the junction of the first and second metatarsal bones.
DU 9 (Zhi yang)	On the posterior midline, in the depression under the spinous process of the seventh thoracic vertebra.
DU 11 (Shen dao)	On the posterior midline, in the depression under the spinous process of the fifth thoracic vertebra.
DU 14 (Da zhui)	On the posterior midline, in the depression under the spinous process of the seventh cervical vertebra.

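### Follow-up ratings and the final prolactin draw are timed from treatment sessions that only the pestle arm has, which leaves the control arm without a matching time point and the assessor blinding unprotected

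*Protocol article*

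**What the plan says.** All references are to the protocol article.

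- **Blinding claim.** The abstract (Methods) states: "This is a 2 parallel-group, assessor-blinded, randomized controlled trial". Section 2.5 adds: "Data collectors and statistical analysts will not know the grouping of patients". It also concedes: "It is a pity that patients and operators could not be blinded in this study".
- **Who rates.** Under section 2.11, evaluation and data collection "will be carried out by members of the research group except the operator".
- **When they rate.** Section 2.11: "The symptoms of milk deficiency and TCM symptoms will be evaluated when the patients are enrolled in the group and after each treatment". It continues: "It will be recorded 6 times". For the laboratory primary outcome, "serum prolactin levels should be measured at the time of entering the group and after the end of whole treatment".
- **What a session leaves behind.** Section 2.6 gives the target intensity: "the strength of the operation should be a slight flush on the skin". ST18 and RN17 are among the points used in every pestle patient. Table 1 places ST18 at the root of the breast and RN17 midway between the nipples.
- **What is rated.** Two of the five items of the primary symptom score (section 2.9, Table 2) concern the breast: filling, graded partly by whether milk flows on squeezing, and siltation. Each is averaged over both sides.
- **What each arm receives.** Control care (section 2.7) is advice on feeding, diet, mood and sleep. The pestle arm adds a 30-minute session once a day for 5 days (section 2.8). No sham is described.

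**The concern.** Two features of the schedule cause trouble together.

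First, the clock for follow-up runs from an event that happens in one arm only. A control patient has no session for a rating to come after, so site staff must choose a time. If they choose differently by arm, ratings and blood samples will sit at different distances from the last feed, from breast stimulation and from delivery. Milk flow, fullness and prolactin can plausibly vary with these, so an arm difference could reflect when patients were measured. An analysis plan cannot repair this once the data are collected.

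Second, the rule sends the assessor to the patient after a session that may leave a visible mark close to the area being scored. Controls would have no such mark. Patients and operators are unblinded, so the assessor is the only masked party at the point of measurement, and one of the two primary outcomes is a subjective score.

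Baseline is a smaller matter of the same kind. It is taken on entering the group, and the text does not place it before the allocation envelope is opened.

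**Working it through.** **1. The schedule set against the arms**

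| Measurement | Anchor in section 2.11 | Pestle arm | Control arm |
|---|---|---|---|
| Baseline score | enrolment | defined | defined |
| Five follow-up scores | after each treatment | 5 sessions | no sessions |
| Baseline prolactin | entry | defined | defined |
| Final prolactin | end of whole treatment | after session 5 | no matching event |

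The stated count reproduces: 1 baseline + 5 follow-up = 6 ratings. The number fits a daily rating over 5 days in both arms, but the time of each follow-up rating is anchored in the pestle arm only.

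**2. The route by which blinding could be broken**

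- A slight flush is the intended strength of treatment (2.6).
- ST18 and RN17 are treated in every pestle patient (2.6, Table 1).
- Ratings follow the session (2.11).
- Breast filling and siltation are scored on both sides (2.9).
- Controls have no session and no sham (2.7).

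Several links are not stated: the interval between session and rating, how long the flush lasts, whether it appears at ST18 and RN17 in particular, who squeezes the breast, and whether treated skin is covered. The route is open, but it is not shown to be used.

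**3. Illustration of size, for the milk-yield item only**

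Inputs from section 2.12: SD 1.23, difference 0.77, two-sided alpha 0.05, beta 0.1, 20% dropout, total 128.

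- The plan's own figure: 2 × [(1.96 + 1.28) × 1.23 / 0.77]² = 53.6 per group, against a stated figure of around 53. It reproduces closely.
- Completers per arm: 128 × 0.8 / 2 = 51.2, taken as 51.
- Table 2 moves in 2-point steps. Assume that unmasking improves the rating by one step in a share p of pestle patients; the mean bias is then 2p. The values of p are assumptions.
- p = 10% gives 0.2 points, and 0.2 / 0.77 = 26% of the planned difference. p = 20% gives 0.4 points, and 0.4 / 0.77 = 52%.
- Standard error of the difference: 1.23 × √(2/51) = 0.2436.
- Noncentrality: 0.2 / 0.2436 = 0.821 and 0.4 / 0.2436 = 1.642.
- Rejection probability of a two-sided 5% t test on 100 degrees of freedom with no true effect: 0.129 and 0.370.

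With 53 per arm the results are 0.132 and 0.382. At p = 5% (0.1 points) and 51 per arm, the result is about 0.07.

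**4. What the illustration does not cover**

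The primary outcome is the 0–28 total score, whose SD is not given, so these rates do not carry over to it. A flush would bear most directly on breast filling, whose SD is also not given. Because that item is averaged over both sides, a one-step change on one side moves it by 1 point, not 2. Nothing in the document allows a size or a direction to be put on the prolactin timing effect.

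**The case against.** The strongest reply is that the article does not say what a stronger reading needs. A reader might infer that blinding fails outright because the assessor inspects a freshly flushed breast. The text gives no interval after the session, so a rating hours later would comply. Table 2 does not say who squeezes. For the points that are knocked, ST18 and RN17 included, section 2.6 gives a separate limit based on what the patient can bear; the flush remark comes later, after the work on the back. Assessors exclude the operator and are said not to know the grouping. All of this stands, and the claim must stop at unprotected and breakable.

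A reader might also infer that both primary outcomes are biased in favour of the pestle needle. That is not supported. Prolactin is a laboratory value that an unmasked rater cannot move, and any timing effect on it has unknown direction.

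It can further be said that section 2.5 uses the word treatment for whichever arm is allocated, and that clock times belong to the full protocol. This has some force for the exact hour. It does not remove the difficulty that the stated anchor, read against sections 2.7 and 2.8, is a recurring session in one arm and general advice in the other.

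On baseline, entering the group may simply mean entering the study. The wording permits rating after allocation but does not show it.

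Finally, several items in Tables 2 and 3 depend on what unblinded mothers report, and the article discloses this limitation. Re-timing would not remove that bias, and a mother may still reveal her group.

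**Conclusion.** The point holds in a limited form. The follow-up ratings and the final prolactin draw are tied to an event that only the pestle arm has, so the schedule gives no matching time point in the control arm. The same schedule leaves the claimed assessor blinding unprotected, since treatment aims at a slight flush, includes points on and beside the breast, and is followed by a score with two breast items. The document does not establish that blinding is in fact broken.

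For the symptom score, both unmasking and timing are possible sources of bias. For prolactin, only timing is, with direction unknown. The illustrative false-positive rates of about 13% and 37%, against a nominal 5%, rest on assumed biases of 0.2 and 0.4 points, no true effect, SD 1.23 and 51 per arm. They apply to the milk-yield item alone, show sensitivity, and do not estimate the actual bias.

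This is a cheap improvement that should be made. It does not invalidate the design.

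**What to change.** In section 2.11, replace the anchor on treatment with times that exist in both arms:

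1. Rate the milk deficiency and TCM scores in both arms at one common clock time each day, set apart from the session, for example before the next day's session. The fifth follow-up rating then falls at the same clock time on the day after the last session.
2. Draw the final prolactin at one common time in both arms, at a set interval from the last feed.
3. State that the baseline score and blood draw are completed before the envelope is opened.

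The cost is re-timing visits already planned. Treatment, number of ratings, assessors and sample size do not change. The drawback is that the immediate post-session effect is no longer captured. Bias from unblinded patients' own reports would remain and should still be acknowledged.

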### Sample size

2.12

The formula of comparison of the mean of 2 samples in completely random design was adopted to calculate the sample size:n1 = n2 = 2[(Zα/2+Zβ) σ /δ]2. We set α at 0.05 (2-sided), β at 0.1, and after looking up the table we get Z α /2 at 1.96, Z β at 1.28. In this study, milk yield was selected as an index to estimate sample size. After consulting the reference,^[22]^ we can get σ at 1.23, δ at 0.77, After calculation, the sample size of each group should be around 53. Considering a dropout rate of 20%, a total of 128 participants will be included in this trial.

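### Section 2.12: with 20% dropout, 128 participants give about 88.5% power for milk yield, not the stated 90%

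*Protocol article*

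**What the plan says.** Section 2.12 (Sample size) uses the usual formula for comparing two independent means, n per group = 2[(Zα/2 + Zβ)σ/δ]². It gives every input:

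- Error rates: "We set α at 0.05 (2-sided), β at 0.1", so the target power is 90%.
- Normal quantiles: "Z α /2 at 1.96, Z β at 1.28".
- Standard deviation and difference, taken from one cited reference: "we can get σ at 1.23, δ at 0.77".
- Endpoint: "milk yield was selected as an index to estimate sample size".

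The result is given as "After calculation, the sample size of each group should be around 53", followed by "Considering a dropout rate of 20%, a total of 128 participants will be included in this trial". The abstract says that participants will be "randomly divided into control group and the pestle needle group in a 1:1 ratio", so 128 means 64 per group. The section does not show how the 20% was turned into 128.

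**The concern.** A dropout allowance should leave the required number of evaluable participants after the stated loss. If a fraction d of those enrolled is lost, the required number must be divided by 1 − d. Multiplying it by 1 + d gives too few. Here 128 looks too small for a requirement of 53 or 54 per group with 20% loss.

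What is at stake is the accuracy of the power statement. A reader of section 2.12 will take it that the trial keeps 90% power for milk yield when one participant in five is lost. If that is not so, the enrolled number, the dropout rate and the power cannot all stand as written.

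**Working it through.** **Inputs** (all from section 2.12, except the 1:1 allocation, which is from the abstract): Zα/2 = 1.96, Zβ = 1.28, σ = 1.23, δ = 0.77, dropout 20%, total 128, so 64 per group.

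**1. Number per group before dropout.**
2 × [(1.96 + 1.28) × 1.23 / 0.77]² = 53.57. Rounded up, 54 are needed. The protocol's figure of about 53 is reproduced apart from the direction of rounding.

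**2. The stated total.**

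| Evaluable per group | Multiplied by 1.2 | Total | Divided by 0.8 | Total |
|---|---|---|---|---|
| 53 | 63.6, so 64 | 128 | 66.25, so 67 | 134 |
| 54 | 64.8, so 65 | 130 | 67.5, so 68 | 136 |

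Only 53 × 1.2, rounded up to 64 per group, gives exactly 128. Against division by 0.8, 128 is 6 participants short (from 53) or 8 short (from 54).

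**3. What remains of 128 after 20% loss.**
128 × 0.8 = 102.4 in total, or 51.2 per group. This step uses only the stated total and dropout rate, so it holds however 128 was obtained.

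**4. Power, by the normal approximation that the protocol uses.**
δ/σ = 0.77/1.23 = 0.626. Power = Φ(0.626 × √(n/2) − 1.96).

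- n = 51: Φ(0.626 × √25.5 − 1.96) = 88.5%
- n = 51.2: 88.6%
- n = 53: 89.7%
- n = 54: 90.2%
- n = 64 (no dropout): 94.3%

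Taking 53 instead of 54 therefore leaves power only about 0.3 points below 90%. The rest of the shortfall comes from the dropout step.

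**5. The same check by t test** (the test that section 2.13 plans for normally distributed measurements).
54 per group gives 89.7% and 51 per group gives 87.9%. On this scale the fall from 54 to 51 is 1.8 points. Comparing 87.9% directly with 90% mixes two methods.

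**6. Detectable difference at 51 per group with 90% power** (protocol's formula, solved for δ).
(1.96 + 1.28) × 1.23 × √(2/51) = 0.79, against the planned 0.77.

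**7. Dropout that 128 can absorb.**
1 − 54/64 = 15.6% keeps 54 per group; 1 − 53/64 = 17.2% keeps 53. With 15% dropout, 64 × 0.85 = 54.4 per group remain, and power is 90.4% by the normal formula.

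**The case against.** The strongest case on the other side is that the effect is too small to matter. Power falls about 1.5 points short, and only if the full 20% is lost. A small change in one assumption has the same effect: with σ = 1.20 instead of 1.23, the formula gives 2 × [3.24 × 1.20 / 0.77]² = 50.99, so 51 per group would be enough. The standard deviation comes from a single reference, and section 2.1 calls the study exploratory. This argument stands as to weight, and it rules out any inference that the trial is seriously underpowered. It does not make the stated figures agree, because the protocol makes a formal power claim that its total does not meet at its own dropout rate.

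It can also be said that the protocol gives 53 only as an approximate figure. That disposes of most of the rounding point, but 51 per group is below 53 as well.

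Three stronger readings are tempting and are not supported:

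- **That the protocol multiplied by 1.2.** The exact match makes this likely, but the step is not printed. The most that can be said is that 128 is consistent with it.
- **That 128 gives roughly this power for the primary outcomes as a whole.** The calculation is for milk yield only, which is one item of the symptom score in section 2.9. No power is calculated for the total score or for serum prolactin.
- **That a baseline-adjusted analysis would recover the loss.** By the approximation n(1 − r²), bringing 53.57 down to 51 needs 1 − r² = 51/53.57 = 0.952, so a baseline-to-outcome correlation r of about 0.22 or more. The document gives no such correlation.

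**Conclusion.** The point holds as a minor arithmetic error. On the protocol's own inputs, 90% power, 20% dropout and 128 participants cannot all be true. With 20% lost, about 51 per group remain, and power for milk yield is about 88.5% by the protocol's formula (87.9% by t test). To keep 90% power at 20% dropout, the total would have to be 136, or 134 if 53 per group is accepted. Most of the gap comes from the dropout allowance and very little from rounding.

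This assumes that the dropout rate is the share of enrolled participants without evaluable data, that losses are equal in the two groups, and that σ = 1.23 and δ = 0.77 are as stated. The cited source for σ and δ was not available and was not checked.

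**What to change.** Keep 128 and restate the last part of section 2.12, for example: *For milk yield, 54 evaluable participants per group are needed (normal approximation); 128 enrolled gives 90% power with up to about 15% dropout and about 88% power with 20% dropout.* The sentence should name milk yield, so that it is not read as a power statement for the other outcomes, and should name the approximation, because 54 per group gives 89.7% by t test.

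The cost is one corrected sentence and a slightly less favourable stated power; recruitment does not change. If the sponsor prefers to keep both 90% power and 20% dropout, the alternative is to enrol 136 (68 per group), which is 8 more participants.

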### Statistical analysis

2.13

We will use SPSS 21.0 software (SPSS Company, Chicago, IL) for statistical analysis. The measurement data will be expressed by mean ±standard deviation. *T* test will be used for measurement data that obey normal distribution, otherwise Mann–Whitney *U* test will be used for analysis. Analysis Of variance will be used In comparing the changes of lactation deficiency symptom and TCM syndrome in different time between test group and control groups. The counting data will be statistically described by frequency, constituent ratio, percentage and so on, and analyzed by Chi-squared test. All the tests in this paper will be 2-sided, and *P* < .05 will be considered statistically significant.

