### Inclusion criteria

2.3

(1)Diagnosis of lactation insufficiency according to the standards for diagnosis and curative effect of Chinese medical symptom criteria.^[18]^(2)Women diagnosed as lactation insufficiency in 48 hours after delivery.(3)Age 20 to 40 years.(4)Women undergoing cesarean section at 37 to 42 weeks of pregnancy.(5)The Apgar score of baby is 8 to 10.^[19]^(6)The length of hospital stay is not less than 7 days to guarantee the completion of 5 treatments.(7)Willing to breastfeed.(8)Sign the informed consent form and volunteer to participate in this study.

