### Primary outcome measurement

2.9

The score of milk deficiency symptom and serum prolactin will be taken as the main outcome indicators. The score of milk deficiency symptom include the evaluation of milk yield, degree of breast filling, degree of milk siltation, the quality of milk, the condition of a baby after breastfeeding (Table 2). The total score was between 0 and 28, and the higher the score was, the more serious the milk deficiency symptom was. Among them, the degree of breast filling and the degree of milk siltation should take the average score according to the situation of both sides of the breast.

**Table 2 T2:** The score of milk deficiency symptom.

	Score			
Item	0	2	4	6
Milk yield	Can fully meet the needs of the baby	Can meet 2/3 of the baby's needs	Can meet 1/3 of the baby's needs	There is almost no milk to feed the baby.
Degree of breast filling	The breasts are full, there is a slight swelling pain, and the milk can flow out without squeezing	The breasts are obviously full, and the milk can flow out with squeezing gently	Breast filling is not obvious, and the milk can flow out with squeezing hard	Breast filling is not obvious, and the milk cannot flow out with squeezing hard
Degree of milk siltation	No milk siltation	Have a feeling of milk distension, and cannot relief after breastfeeding.	The breast has tenderness	Persistent pain caused by milk siltation
The quality of milk	Thick	Clear	No milk	
The condition of a baby after breastfeeding	The baby sleeps quietly between 2 breastfeeding.	The baby sleeps a little quieter between 2 breastfeeding.	The baby cries between 2 breastfeeding.	There is almost no milk to feed the baby.

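### Serum prolactin, a primary outcome measured at entry and at the end, gets only a covariate-free two-sample test of an undefined quantity; adjusting for the entry value is at least as precise on either reading

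*Protocol article*

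**What the plan says.** All references are to the protocol article.

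- Section 2.9 (Primary outcome measurement): "The score of milk deficiency symptom and serum prolactin will be taken as the main outcome indicators".
- Section 2.11 (Data collection and management): "subject's serum prolactin levels should be measured at the time of entering the group and after the end of whole treatment". Each woman therefore has one entry and one end value. The two symptom scores are recorded six times, at entry and after each of five treatments.
- Section 2.13 (Statistical analysis) sets the rule for continuous data: a t "test will be used for measurement data that obey normal distribution", and the Mann–Whitney U test otherwise. Analysis of variance is planned for "comparing the changes of lactation deficiency symptom and TCM syndrome in different time between test group and control groups", a sentence that leaves prolactin out. No covariate is named in either sentence.
- Section 2.12 (Sample size): "We set α at 0.05 (2-sided), β at 0.1". The standard deviation (1.23) and difference (0.77) are for milk yield. Nothing is given for prolactin.

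**The concern.** Section 2.13 never names prolactin. The analysis of variance is limited to the two scores, so by elimination prolactin falls under the generic two-sample rule. That rule leaves two things unsettled or unused for a primary outcome: the quantity compared (end value or change) is not defined, and the entry measurement is not used as a covariate although every woman is to have it.

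At stake is the width of the confidence interval for a primary outcome whose power the protocol never works out, since the sample size rests on milk yield alone. Leaving the quantity open also allows the choice between end value and change to be made after the data are seen.

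**Working it through.** **Inputs.** From section 2.12: two-sided α 0.05, β 0.1, σ 1.23, δ 0.77 (milk yield), 20% dropout, 128 women in total. Allocation is 1:1 (abstract). Assumed: r, the correlation between entry and end prolactin, at 0.3, 0.5 and 0.7, and equal variance at the two times.

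**The plan's own figure.** n per arm = 2[(1.96 + 1.28) × 1.23 / 0.77]² = 53.57, stated as about 53. Then 53 × 1.2 = 63.6, rounded up to 64 per arm, or 128 in total. The stated size reproduces. If 20% of 64 are lost, 64 × 0.8 = 51.2, so about 51 per arm remain, which is the base used below.

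**Variance of the between-arm difference, relative to end values:**

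- t test on end values: 1
- t test on change from entry: 2(1 − r)
- ANCOVA on entry value: 1 − r²

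Because 1 − r² = (1 − r)(1 + r), the ratio of ANCOVA to change is (1 + r)/2, which is never above 1. ANCOVA is also never above end values, because 1 − r² ≤ 1. Change is worse than end values whenever r < 0.5.

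| r | Change, 2(1−r) | ANCOVA, 1−r² | Cut against end values | Equivalent extra patients, 1/(1−r²) − 1 |
|---|---|---|---|---|
| 0.3 | 1.40 | 0.91 | 9% | 10% |
| 0.5 | 1.00 | 0.75 | 25% | 33% |
| 0.7 | 0.60 | 0.51 | 49% | 96% |

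**Illustrative power.** The only standardised effect available is 0.77/1.23 = 0.626, for milk yield. Power is from the noncentral t distribution at 51 per arm, with the effect divided by the square root of the variance factor:

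| r | End values | Change | ANCOVA |
|---|---|---|---|
| 0.3 | 87.9% | 75.4% | 90.7% |
| 0.5 | 87.9% | 87.9% | 95.1% |
| 0.7 | 87.9% | 98.1% | 99.2% |

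The extra degree of freedom used by the covariate does not alter these figures at one decimal place. They concern the t test; the Mann–Whitney test, which also takes no covariate, was not computed.

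**The case against.** **The test may already use the entry value.** A reader might infer that the plan discards entry prolactin. The text does not support that: a t test on change would use it, and section 2.13 does not say which is meant. At r = 0.7 a change-score test already reaches 98.1% in the illustration, against 99.2% for ANCOVA. This stands, so the point is confined to what is true on both readings: the quantity is undefined, and neither version is more precise than ANCOVA.

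**Chance imbalance is not a second fault.** A reader might infer that a baseline difference between arms biases the result. Allocation is randomised, so the unadjusted test is unbiased with valid type I error. The part of a chance baseline difference that carries into end values is the same r² share of variance that ANCOVA removes. Listing it separately would count the loss twice.

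**The size is not known.** The protocol gives no r, standard deviation or target difference for prolactin. At r = 0.3 the gain is under 3 percentage points of power, and the study calls itself exploratory. This also stands, and limits how hard the point can be pressed.

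**Time since delivery.** It is tempting to ask for hours from delivery to randomisation as a further covariate, because section 2.3 admits "Women diagnosed as lactation insufficiency in 48 hours after delivery". That criterion dates the diagnosis and leaves the time of randomisation open. Section 2.11 does not list the interval among the collected data, and nothing shows it would add precision.

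**A detail for a fuller document.** Covariates are often left to the full protocol or analysis plan. Here, however, the article itself names the test, so the comment is on a stated choice.

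**Conclusion.** The point holds as a matter of precision. On either reading of section 2.13, the two-sample test of prolactin is no more precise than a baseline-adjusted analysis of data already planned. Relative to end values, the variance given up is 9%, 25% or 49% for assumed r of 0.3, 0.5 or 0.7. Relative to change scores it is 35%, 25% or 15%, from 1 − (1 + r)/2. These fractions assume equal variances at the two times and a linear relation. The power figures further assume that the milk-yield effect size applies to prolactin and that 51 women per arm are evaluable, so they illustrate and do not predict. No conclusion of the trial would become invalid if the plan stayed as it is. The change is nevertheless worth making, because prolactin is a primary outcome, the entry sample is already scheduled, and the present wording leaves the analysed quantity open.

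**What to change.** In section 2.13, before outcome data are examined by arm:

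1. State that the main prolactin analysis is a linear model (ANCOVA) of end-of-treatment prolactin on arm and entry prolactin, on the log scale if the values are skewed.
2. Report the adjusted difference, or the adjusted ratio on the log scale, with a 95% confidence interval.
3. Keep the t test or Mann–Whitney test as a sensitivity analysis, and say whether it uses end values or change.
4. For the two symptom scores, keep the analysis over time of the five post-treatment records, with the entry score as a covariate and not as one of the compared outcomes. Replacing it by an ANCOVA of the last record alone would drop the four intermediate assessments.

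The cost is a few sentences. No new measurements or patients are needed, and the SPSS package already named in the plan fits these models.

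### Section 2.13 plans no baseline adjustment although baseline is collected for every outcome; the tests are valid but give up precision, and the ANOVA over time yields no stated treatment difference

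*Protocol article*

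**What the plan says.** All places are in the protocol article.

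- Section 2.11 has milk deficiency symptoms and TCM symptoms scored at enrolment and after each of the five treatments, six recordings in all. For the other primary outcome, "serum prolactin levels should be measured at the time of entering the group and after the end of whole treatment". Both primary outcomes and the secondary outcome therefore have a baseline value.
- Section 2.13 says that the t test "will be used for measurement data that obey normal distribution", with the Mann-Whitney U test otherwise. For the repeated scores, "Analysis Of variance will be used In comparing the changes of lactation deficiency symptom and TCM syndrome in different time" between the two groups. It names no covariate. It does not say whether enrolment is one of the ANOVA time levels, or which ANOVA term answers the treatment question.
- Section 2.12 sizes the trial without adjustment: "The formula of comparison of the mean of 2 samples in completely random design was adopted to calculate the sample size". The inputs are "We set α at 0.05 (2-sided), β at 0.1" and "we can get σ at 1.23, δ at 0.77", and "milk yield was selected as an index to estimate sample size".

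**The concern.** When an outcome is measured before randomised treatment and again afterwards, the baseline value usually predicts the later one. Adjusting for it removes that part of the variance and corrects the estimate for whatever imbalance chance has produced. The article commits to specific tests that do neither.

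The symptom scores raise a second issue. Enrolment precedes any treatment effect. If it enters the ANOVA as one of six outcome levels, the group main effect averages in a recording at which the true difference is zero. The group-by-time term avoids that dilution but tests five degrees of freedom at once, so it shows that the profiles differ without saying by how much.

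At stake are the width of the confidence interval, exposure to chance imbalance, and whether the symptom-score analysis ends in a treatment difference that a clinician can read.

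**Working it through.** **Inputs from section 2.12:** δ = 0.77, σ = 1.23, two-sided α = 0.05, β = 0.1, 20% dropout, 128 in total. **Assumed:** the baseline-to-follow-up correlation ρ, which the document does not give, taken as 0.3, 0.5 and 0.7.

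**1. The plan's own figure.** n = 2[(1.96 + 1.28) × 1.23 / 0.77]² = 53.57 per arm, which agrees with "the sample size of each group should be around 53". The total follows as 53 × 1.2 = 63.6, rounded to 64 per arm and 128 in all. A 20% loss from 64 leaves 64 × 0.8 = 51.2, so 51 per arm is used below.

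**2. Unadjusted comparison after treatment.** d = 0.77 / 1.23 = 0.626. The noncentrality is 0.626 × √(51/2) = 3.16 on 100 df, which gives power of 87.9%.

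**3. ANCOVA.** The residual SD is σ√(1 − ρ²), so d becomes 0.626 / √(1 − ρ²).

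**4. Change from baseline, if that is what section 2.13 means by changes.** The SD is σ√(2(1 − ρ)), so d becomes 0.626 / √(2(1 − ρ)).

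| Assumed ρ | Unadjusted | Change score | ANCOVA | n per arm for 90% power, ANCOVA |
|---|---|---|---|---|
| 0.3 | 87.9% | 75.4% | 90.7% | 49 |
| 0.5 | 87.9% | 87.9% | 95.1% | 41 |
| 0.7 | 87.9% | 98.1% | 99.2% | 28 |

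The last column is 53.57 × (1 − ρ²), rounded up, against 54 unadjusted. Since 1 − ρ² = (1 − ρ)(1 + ρ) is smaller than 2(1 − ρ) whenever ρ < 1, change scores stay below ANCOVA throughout.

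**5. Chance imbalance.** With 51 per arm, the difference in baseline means has a standard error of √(2/51) = 0.198 SD. A gap of that size moves the unadjusted final difference by ρ × 0.198 SD. At ρ = 0.5 this is 0.099 SD, about 16% of the planned effect (0.099 / 0.626).

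**6. Enrolment as an ANOVA level.**
- If the full effect is present from session 1, the main effect over six recordings is 5/6 × 0.77 = 0.64.
- If the effect builds linearly over five sessions, the mean of 0, 0.2, 0.4, 0.6, 0.8 and 1 is 0.5, so the main effect is 0.385.
- With six levels and two groups, group-by-time has 5 × 1 = 5 df.

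**The case against.** The strongest reply is that nothing here is invalid. A t test or Mann-Whitney test between randomised groups is sound, and section 2.12 sized the trial for an unadjusted comparison of means. The 90% target was never built on adjustment, so its absence does not undermine it. The gain depends on a correlation that the document does not give; it is about 3 points at 0.3 and nil at zero. All of this stands.

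Four stronger readings are tempting, and the document does not support them.

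- **The ANOVA is badly underpowered.** Under linear build-up with enrolment included, the group main effect has only 60% to 40% power for equal correlation of 0.4 to 0.8 (51 per arm). But comparing changes over time between groups reads more naturally as the group-by-time term. Its noncentrality is (51/2) × 0.7 × 0.626² / (1 − ρ) on 5 and 500 df, which gives 75% to 99.9% over the same range. Section 2.13 also does not say that enrolment is a level.
- **Women with a missed day are discarded.** The article specifies neither classical repeated-measures ANOVA nor complete cases, and such detail may sit in a fuller plan.
- **The normality rule costs power on milk yield.** In a simulated four-level item the Mann-Whitney test had 86.2% power against 87.4% for the t test, about one point. Section 2.9 also defines the primary outcome as the 0 to 28 total, not that item.
- **No outcome has a single effect estimate.** Prolactin has one post-treatment value, so a t test there gives one mean difference.

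**Conclusion.** The point holds as a matter of efficiency and of a clearly stated treatment effect. It does not show that inference is invalid or that the trial misses its planned power. Section 2.13 leaves unused a baseline that the trial already collects. At 51 per arm, ANCOVA would raise power from about 88% to 91%, 95% or 99% at correlations of 0.3, 0.5 or 0.7, and would remove the effect of chance imbalance. Reading the ANOVA as an analysis of change scores does use baseline, but less efficiently, and at 0.3 it does worse than ignoring baseline.

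For the symptom scores only, the ANOVA offers either a main effect that may be diluted or a 5-df p-value, and the text does not say which one decides.

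The figures rest on the section 2.12 effect and SD, which belong to milk yield. They illustrate, but do not establish, the gain for the total symptom score or prolactin. The correlation is an assumption throughout. This change should be made, but the trial does not depend on it.

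**What to change.** Amend section 2.13, or the analysis plan, before group codes are released:

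- **Symptom scores (milk deficiency and TCM):** a linear mixed model of the five post-baseline recordings with group, day, group-by-day and baseline score as covariate. The reported effect is the baseline-adjusted group difference after session 5 with its 95% confidence interval. Enrolment is then a covariate and cannot be an outcome level.
- **Serum prolactin:** ANCOVA of the final value on baseline value and group, with the adjusted difference and 95% confidence interval.
- **Choice of test:** fix these models in advance instead of selecting by a normality check, and keep the Mann-Whitney test as a sensitivity analysis.
- **TCM syndrome type:** add it as a covariate only if it is recorded before randomisation in both groups. Section 2.6 uses it to choose additional acupoints for the needle treatment, and nothing in the article shows that controls are typed.

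No new data or patients are needed, and the planned SPSS software can fit both models. The cost is a few sentences and a slightly more complex model to explain.
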